## Abstract

**Background:**

While older adults (age 75 and over) represent a large and growing proportion of patients with acute myocardial infarction (AMI), they have traditionally been under-represented in cardiovascular studies. Although chronological age confers an increased risk for adverse outcomes, our current understanding of the heterogeneity of this risk is limited. The Comprehensive Evaluation of Risk Factors in Older Patients with AMI (SILVER-AMI) study was designed to address this gap in knowledge by evaluating risk factors (including geriatric impairments, such as muscle weakness and cognitive impairments) for hospital readmission, mortality, and health status decline among older adults hospitalized for AMI.

**Methods/Design:**

SILVER-AMI is a prospective cohort study that is enrolling 3000 older adults hospitalized for AMI from a recruitment network of approximately 70 community and academic hospitals across the United States. Participants undergo a comprehensive in-hospital assessment that includes clinical characteristics, geriatric impairments, and health status measures. Detailed medical record abstraction complements the assessment with diagnostic study results, in-hospital procedures, and medications. Participants are subsequently followed for six months to determine hospital readmission, mortality, and health status decline. Multivariable regression will be used to develop risk models for these three outcomes.

**Discussion:**

SILVER-AMI will fill critical gaps in our understanding of AMI in older patients. By incorporating geriatric impairments into our understanding of post-AMI outcomes, we aim to create a more personalized assessment of risk and identify potential targets for interventions.

**Trial registration:**

Trial registration number: NCT01755052.

## Background

Among patients hospitalized for acute myocardial infarction (AMI), one-third are 75 years or older [1]. The number of incident AMI cases in this age group is expected to double over the next 30 years as the mean age of the general population increases [2], yet this group has been under-represented in AMI clinical trials and epidemiologic studies [3]. This group is fundamentally different from younger patients with AMI: they have a higher burden of comorbid diseases and aging-related physical and cognitive impairments, as well as lower physiologic reserve. Results from studies of younger patients with AMI may therefore not be directly applicable to this growing population.

While advanced age is a risk factor for adverse outcomes after AMI [1], there is great heterogeneity among older patients and chronological age is a relatively crude indicator of physiological age [3,4]. Despite emerging interest in understanding the role of geriatric conditions (such as physical and cognitive impairments) as they pertain to cardiovascular outcomes [3], the majority of studies examining risk have used administrative datasets that lack this information [5], and none of the currently available risk stratification tools for AMI incorporate geriatric conditions. Furthermore, these risk models have only modest discrimination in older patients [6,7], and were designed solely to predict clinical events (i.e., mortality, reinfarction) rather than patient-centered outcomes, such as health status.

The Comprehensive Evaluation of Risk Factors in Older Patients with AMI (SILVER-AMI, R01HL115295, PI [name]) study was designed to address these knowledge gaps by melding principles from geriatrics and cardiology with the goal of more precisely characterizing the risk of traditional clinical events, as well as patient-centered outcomes, in older adults with AMI. The primary objective is to generate risk models that predict all-cause readmission, all-cause mortality, and decline in health status, that exceed the capabilities of currently available risk models in older adults. We hypothesize that the incorporation of geriatric conditions will lead to better discrimination than existing risk models. Secondary objectives are to: (1) estimate the frequency and determinants of adverse post-hospital events important in this population, including medication side effects, symptoms, falls, and bleeding; and (2) describe AMI processes of care (e.g. door-to-balloon time, revascularization strategies, use of secondary prevention medications). We believe that achieving these objectives can inform complex post-AMI decision-making in older adults (Figure 1). The purpose of this article is to describe the design, rationale, and methods of the SILVER-AMI study.

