### Statistical analysis

The primary outcomes of SILVER-AMI are the occurrence of all-cause hospital readmission, all-cause death, and decline in health status within six months of hospital discharge. Using independent risk factors that include cardio-centric factors (e.g. STEMI vs. NSTEMI, systolic blood pressure, Killip Class), as well as geriatric impairments, we will construct risk stratification models that predict the probability of each outcome for specific combinations of the risk factors. These models will be variants of the Cox regression models for the time-to-event outcomes (hospital readmission and mortality) and the logistic model used for decline in health status. Because mortality serves as a competing risk for hospital readmission, we will evaluate the associations of explanatory variables with both time-to-event outcomes using the competing risk approach of Fine and Gray [27]. All linearity assumptions will be checked graphically and deviations from model additivity will be accommodated by an examination of all statistically significant, clinically indicated two-factor interactions. All missing data will be examined for the nature of missingness, i.e., whether missing at random, and if justifiable, multiple imputation will be applied. Models will be evaluated with an examination of residuals and goodness-of-fit statistics using SAS/STAT ® V9.3 (SAS Institute, Cary, NC) or later, with statistical significance defined as a two-sided p-value <0.05.

Internal and external validation techniques will then be used to test the reproducibility of the risk stratification tools. For internal validation, jackknife methods [28] will be used to evaluate the percent of correct classification; external validation will be performed on the 500 randomly selected participants who were excluded from both model building and internal validation.

Once the final models have been developed, user-interface applications will be developed for “smart-phones” and other hand-held devices. The model coefficients for each outcome will be stored in hand-held applications whose outputs will provide the probability of each outcome. The inputs to the applications will consist of simple yes/no entries denoting the presence or absence of risk factors. Calculation will be presented in real time, and the results will list specific risk factors, and probability of the outcomes.

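### The hypothesis credits geriatric conditions with a gain over existing risk models, a comparison that cannot separate their contribution from refitting and other new predictors

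*Protocol article*

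**What the plan says.** The Background of the protocol article gives a primary objective and a hypothesis. The objective is to produce models for readmission, death and health status decline "that exceed the capabilities of currently available risk models in older adults". The hypothesis follows directly: "We hypothesize that the incorporation of geriatric conditions will lead to better discrimination than existing risk models". The cause it names is geriatric conditions, and the comparator it names is existing risk models.

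The Background describes that comparator in three ways:
- on content, "none of the currently available risk stratification tools for AMI incorporate geriatric conditions";
- on performance, "these risk models have only modest discrimination in older patients";
- on purpose, they "were designed solely to predict clinical events (i.e., mortality, reinfarction) rather than patient-centered outcomes, such as health status".

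The Statistical analysis section describes how the new models are built: "Using independent risk factors that include cardio-centric factors", and then "as well as geriatric impairments, we will construct risk stratification models that predict the probability of each outcome". Cardiac and geriatric factors therefore enter together. Validation uses a jackknife within the development set and 500 participants drawn at random from the same cohort of 3000.

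**The concern.** A new model can differ from a published score in three ways. Its clinical weights are re-estimated in this older cohort. It can use sociodemographic and medical-record predictors that the score lacks. It includes geriatric conditions. The hypothesis concerns only the third, but the named comparison measures all three together.

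The article itself gives a reason to expect a gain from the first. It says that older patients differ fundamentally from younger ones and that existing models discriminate only modestly in them. Validation on a random split of the same cohort does not remove this advantage, because the 500 come from the population in which the weights were refitted.

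At stake is the study's main message. The Discussion presents geriatric assessment as a route to more personal risk estimates, and calculators for hand-held devices are planned. If a gain over a published score came from refitted clinical variables, it could be read as evidence for cognitive, grip and mobility testing when it is not.

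**Working it through.** **1. The plan's own figures.** These reproduce but do not bear on the point.
- Deaths in the validation set: 500 × 0.28 = 140, as stated.
- Deaths in the development set: 2500 × 0.28 = 700. Power for a relative risk of 1.3 is Φ(√(700·p·(1−p))·ln 1.3 − 1.96). With prevalence p = 0.30: √147 × 0.2624 − 1.96 = 1.22, or 88.9%. With p = 0.50: √175 × 0.2624 − 1.96 = 1.51, or 93.5%.
- Readmissions: 2500 × 0.39 = 975 events, giving 96.4% and 98.4%.

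The stated 90% is therefore about right. It is power for the relative risk of a single predictor, not for a difference in discrimination.

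**2. Null geriatric effect, varying the fit of the published weights.** From the article: 2500 development and 500 validation participants, and 28% events. Assumed: 12 clinical predictors, 10 geriatric predictors with zero effect, a clinical linear predictor with SD 0.8 or 1.0, and a logistic outcome. The published score uses the same 12 predictors, with weights correlated ρ with the true ones. Significance is by a paired DeLong test in the 500. Ranges cover the two SDs, and repeat runs moved them by a few percentage points.

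| ρ | New model numerically ahead of published score | Significantly ahead |
|---|---|---|
| 1 | 16-21% | under 1% |
| 0.95 | 60-74% | about 5% (5-10% in a repeat) |
| 0.9 | 80-94% | 13-29% |
| 0.8 | 96-98% | 47-68% |

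At ρ = 0.9 the c-statistics are about 0.68-0.72 for the published score and 0.70-0.74 for the new model. Against a clinical-only model refitted in the same 2500, the same null-geriatric model is ahead in 22-30% of runs, and significantly so in about 1% or fewer.

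**3. A second set-up that adds non-geriatric predictors and a real effect.** Assumed: 8 cardiac predictors with coefficient 0.25 each; 4 further non-geriatric predictors with coefficient 0 or 0.2; 8 geriatric conditions at 35% prevalence with odds ratio 1 or 1.3; about 29% events; 300 runs per case. Published weights are 0.25 ± m, so their correlation with the truth is 0.25/√(0.25² + m²): 0.93 for m = 0.1 and 0.78 for m = 0.2.

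| Geriatric OR | Extra predictors | m | New minus published (c) | New ahead | With minus without geriatric (c) |
|---|---|---|---|---|---|
| 1 | no | 0 | −0.008 | 19% | −0.003 |
| 1 | no | 0.1 | +0.006 | 69% | −0.003 |
| 1 | no | 0.2 | +0.035 | 96% | −0.003 |
| 1 | yes | 0 | +0.020 | 88% | −0.003 |
| 1 | yes | 0.1 | +0.034 | 96% | −0.003 |
| 1 | yes | 0.2 | +0.061 | 100% | −0.002 |
| 1.3 | no | 0 | +0.016 | 86% | +0.020 |
| 1.3 | yes | 0.1 | +0.052 | 99% | +0.017 |

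The gain over the published score runs from −0.008 to +0.061 with no geriatric effect, and from +0.016 to +0.052 with a real one. The second range lies wholly inside the first, so the size of that gain does not show which case holds. The last column does: it stays just below zero in all six null cases and is clearly positive in the other two.

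**The case against.** **Existing tools are the right benchmark for the stated objective.** This stands. The objective is to exceed available models, and for that a published score is the proper comparator. The difficulty lies only in the next sentence of the article, which names geriatric conditions as the source of the gain.

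**The article fixes no decision rule, and an unseen protocol or analysis plan may contain a nested comparison.** This also stands, and a reader should not infer that such an analysis is missing. The point concerns the hypothesis as published, which pairs a named cause with a comparator that cannot isolate it.

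**The multivariable coefficients would expose uninformative geriatric terms.** This is partly right. With 10 null terms tested at 0.05, the expected number significant is 10 × 0.05 = 0.5, and none is significant with probability about 0.95^10 = 0.60. A simulation of the set-up in step 2 gave about 0.5 terms on average and none in 55-63% of runs. That leaves 37-45% of runs with at least one spurious term. More importantly, a significant coefficient shows association; it does not measure how much discrimination the geriatric conditions add, which is what the hypothesis claims.

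**The weight correlation is assumed, and modest performance in older patients could itself reflect the missing geriatric information.** This stands. The article does not identify the correlation, and the rates depend heavily on it.

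**Conclusion.** The point holds as one about attribution. A gain over existing models would fit the objective but could not be credited to geriatric conditions. With uninformative geriatric terms and some mismatch in the published weights, a numerical advantage is likely (about 60-74% at correlation 0.95, rising to 96-98% at 0.8). Statistical significance is much less common under mild mismatch (about 5% at 0.95 and 13-29% at 0.9).

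Two stronger readings are tempting, and the article supports neither:
- *A new model is bound to beat a published score.* It is not: with optimal published weights and no other new predictors it is ahead in only about 16-21% of runs.
- *The hypothesis can be neither confirmed nor refuted.* Failing to beat existing models would count against the sentence as written. What the comparison cannot do is say how much of any gain is geriatric.

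The percentages rest on the assumed numbers of predictors, effect sizes and weight correlations. They also use logistic models, whereas the plan uses Cox-type models for two of the three outcomes. The structural argument does not depend on these choices.

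For health status decline the named comparator may not exist, since the article says that existing models were not designed for that outcome.

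**What to change.** Word the hypothesis as a nested contrast and carry it into the Statistical analysis section. For each outcome:
1. In the same 2500, fit a model with the cardio-centric, clinical and sociodemographic factors, and then the same model plus the geriatric conditions.
2. Test the geriatric conditions jointly as one block, by a likelihood-ratio or Wald test.
3. In the 500, report the difference in c-statistic between the two models with its confidence interval.
4. Credit only that difference to geriatric conditions.

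The block test should carry the inference. In the null simulations, the DeLong comparison of the two nested models favoured the larger one significantly in about 1% of runs or fewer, below the 2.5% expected in that direction.

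Keep the comparison with published scores as a separate benchmark for the primary objective, where such a score exists for the outcome.

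The cost is one more model fit per outcome on data already being collected, plus some rewording. The downside is that the gain credited to geriatric conditions will probably be smaller than the gain over a published score.

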**Figure 1 Fig1:**
[figure not shown]
**Comprehensive assessment to inform post-AMI decision making in older adults.** Assessment of multiple domains may optimize medical decision-making. (For clarity, not all possible risk factors or post-AMI clinical decisions are listed).

## Methods/Design

SILVER-AMI is a multi-center, longitudinal cohort study in which participants undergo a comprehensive baseline (in-hospital) assessment, and then complete a follow-up telephone interview (six months after discharge). The study received approval from the Yale Institutional Review Board (IRB), as well as IRBs at the participating study sites, and is registered at www.clinicaltrials.gov (NCT01755052, registered 11/27/2012).

### Study sites: management and training

The recruitment network for SILVER-AMI was assembled with the goal of reflecting a wide geographic distribution and a diverse mix of practice types. There are approximately 70 recruitment sites located in the United States representing 27 states (Figure 2). The SILVER-AMI network is built upon the foundation of the recruitment network assembled for the VIRGO study [8] and additional sites were recruited through the American College of Cardiology’s Section of Geriatric Cardiology. The majority of sites (71.4%) are non-academic hospitals. Hospitals are heterogeneous in size (range: 83 to 2292 beds, median 475) and location (urban: 47.1%, suburban/rural: 52.9%).

**Figure 2 Fig2:**
[figure not shown]
**SILVER-AMI national recruitment network.**

Each site identifies a site research coordinator who has primary responsibility for implementing the study protocol. Prior to study initiation, the site research coordinators complete required trainings (in the recruitment of older hospitalized patients, obtaining of informed consent, and use of the electronic data capture system) conducted by the Yale Coordinating Center, and are supplied with standardized equipment to perform the physical assessments.

### Patient screening and determination of eligibility

Screening is performed in the hospital setting by the site research coordinators who review daily admission records to identify potentially eligible participants. Site research coordinators then perform a medical record review to confirm eligibility in accordance with the criteria found in the Third Universal Definition of Myocardial Infarction [9], listed in Table 1.

### In-hospital assessment

Participants undergo an interview and physical assessment by the site research coordinator during their baseline AMI hospitalization (Table 2). In addition to sociodemographic and presentation characteristics, specific domains are tested which are described below. Participants receive a $25 gift card for completing this assessment.

**Table 2 Tab2:** **Domains and timing of assessments in SILVER-AMI**

**Domain (Instruments)**	**Baseline interview**	**Medical record abstraction**	**Six-month interview**	**Six-month event review**
Sociodemographic characteristics (race, marital status, education, income)	x			
Clinical characteristics				
Presenting symptoms	x	x		
Cardiac history		x		
Non-cardiac comorbidities		x		
In-hospital medications		x		
Procedures (cardiac catheterization, PCI, CABG, pacemaker, ICD)		x		x
In-hospital cardiac testing (echo, stress test)		x		
In-hospital complications		x		
Discharge medications		x		
Discharge disposition		x		
Health status measures, symptom burden, psychosocial assessments				
General health (SF-12)	x		x	
CAD-specific health (SAQ-7)	x		x	
General symptoms (ESAS)	x		x	
Social support (MOS-SSS)	x			
Comprehensive geriatric assessment				
Depressive symptoms (PHQ-8)	x		x	
Cognition (TICS, COWAT)	x			
Vision and hearing	x			
Grip strength (dynamometer)	x			
Functional mobility (TGG)	x			
Activities of Daily Living	x		x	
Fall assessment	x		x	
Delirium (abbreviated CAM)	x		x	
Orthostatic vital signs	x			
Alcohol and tobacco frequency	x			
Post-discharge health care utilization				
Emergency Department visits				x
Hospital readmissions				x
Cardiac procedures				x
Medication adverse effects				x
Medication adherence				x
Deaths				x

*Abbreviations:*
*PCI* percutaneous coronary intervention, *CABG* coronary artery bypass grafting, *ICD* implantable cardioverter defibrillator, *SF-12* Short-Form 12, *CAD* coronary artery disease, *SAQ-7* abbreviated Seattle Angina Questionnaire, *ESAS* Edmonton Symptom Assessment Scale, *MOS-SSS* Medical Outcomes Study Social Support Scale, *PHQ-8* Patient Health Questionnaire, *TICS* Modified Telephone Interview for Cognitive Status, *COWAT* Controlled Word Association Test, *TGG* Timed Get Up and Go, *CAM* Confusion Assessment Method.

#### Health status measures, symptom burden, and psychosocial assessments

Participants are asked about health status with the Short Form 12 (SF-12) [11], a widely used health status measure that has demonstrated reliability and validity in many populations, including older adults. In addition, dimensions of health status specific to coronary artery disease are assessed with the abbreviated Seattle Angina Questionnaire (SAQ) [12] which measures three angina-related domains: physical limitation, angina frequency, and quality of life.

Symptoms are assessed with the Edmonton Symptom Assessment Scale (ESAS) [13], a visual analogue scale that contains nine common symptoms (pain, fatigue, nausea, depression, anxiety, drowsiness, appetite, well-being, shortness of breath) that are rated by participants on a severity scale of 1 (no symptoms) to 10 (worst possible symptoms).

Depression is known to be prognostically important in patients with cardiovascular disease; [14] we therefore assess depressive symptoms with the eight-item Patient Health Questionnaire (PHQ-8) [15]. In addition, a shortened five-item version of the Medical Outcomes Study Social Support Scale (MOS-SSS) evaluates perceived social support [16].

#### Geriatric conditions

General cognitive function is evaluated with the Telephone Interview of Cognitive Status (TICS) [17]. We chose the TICS because it can be administered in <10 minutes, can be used to detect mild as well as severe cognitive impairments, does not require writing (i.e. can be used despite visual or motor impairments), and can be converted to a Mini Mental State Examination (MMSE) equivalent [18]. In addition to general cognitive function, we include an assessment of executive function, which is relevant for specific tasks such as adherence to complex medical regimens after discharge, with the Controlled Word Association Test (COWAT) [19].

Vision questions are adapted from the Visual Functioning Questionnaire (VFQ-25); [20] participants are asked to rate their general vision on an ordinal scale (from “excellent” to “very poor”), and to indicate whether they have difficulty reading print or doing work or hobbies. Hearing is assessed with a global question (“do you have a hearing problem now?”) that has shown good sensitivity and specificity compared with audiography [21].

Muscle strength and functional mobility are important predictors of future disability and health status decline [22,23]. For muscle strength we chose to measure grip strength, which is assessed by the participant using their dominant hand to squeeze a handheld dynamometer (B&L Engineering, Santa Ana, CA); results are recorded in kilograms (kg) for three successive attempts. Functional mobility is measured with the Timed Get Up and Go (TUG) test [23], which requires the participant to rise from a seated position, walk 3 meters, and then return to the chair and sit down. The time it takes to complete this test in seconds is recorded, as well as a subjective rating of the person’s movements on a scale of 1–5 from normal to severely abnormal.

Activities of Daily Living (ADLs) [24] are measured with four interview items that assess whether participants are able to perform, without help from another person, the tasks of bathing, dressing, getting out of a chair, and ambulating. Participants are also asked how many falls they have had in the past year (from none to ≥ four).

